## Outcomes

### Assessments

Prior to the initial assessment, the assessor will obtain written consent from the participant. Baseline descriptive characteristics will be collected at T0 and include biological sex, age, weight, height, body mass index, education level, characteristics of stroke, and past medical history. Additionally, the degree of neurological deficit (National Institutes of Health Stroke Scale, NIHSS [60]), upper limb motor function (Chedoke McMaster Stroke Assessment, CMSA [61]), and global cognitive function (Montreal Cognitive Assessment [62]) will be assessed at baseline. Medication use will be recorded at all time points. PASIPD [59] will be assessed at all time points and midway through the 8-week follow-up (week 16), to account for changes in physical activity between T1 and T2. All outcomes, apart from enjoyment, will be collected T0–T2 at both sites. To minimize participant fatigue, assessments will take place over 3 days (1.5 h each). Data collection forms can be provided by study PIs upon request. Figure 3 provides a timeline and collection of outcomes.

**Fig. 3 Fig3:**
[figure not shown]
Schedule of enrolment, interventions, and assessments

### Primary outcome

#### Neuroplasticity

Our study will assess changes in neuroplasticity with TMS applied to the representational areas of the hand’s first dorsal interosseous muscle (FDI) on M1. We selected this muscle because it can be elicited at relatively low stimulation intensities that are more comfortable for the participant [63] and because it is involved in upper limb activities of daily living such as grasping objects. We will also apply TMS on both hemispheres [21, 22], so that we can assess whether exercise will restore imbalances in interhemispheric excitability, an important marker of motor recovery after stroke [44].

##### General TMS procedures

Electromyography will be recorded from the FDI on the participant’s affected and unaffected sides. The position of electrodes will be photographed (with permission from the participant), to ensure repeatability in all assessments (T0–T2). Using neuronavigation (Brainsight, Rogue Research), we will co-register the heads of participants to a generic MRI template to identify and mark optimal areas for stimulation (a “hotspot”) on M1 to elicit a motor-evoked potential (MEP). The amplitude of the MEP will indicate the level of muscle activation in response to TMS, used to quantify excitability. Neuronavigation software will allow us to save the “hot-spot” of each person in order to repeat the stimulation with better spatial accuracy [64]. Once the “hot-spot” has been identified, we will determine the resting motor threshold (RMT), the minimum intensity to obtain 10 MEPs with an amplitude of 0.05μm out of 20 stimulations [63]. Electrical stimulation over the median nerve (FDI) will be used to assess changes in muscle contractility. This assessment has been demonstrated to be feasible for patients with stroke [65], and our laboratory has shown that normalizing MEP amplitude to muscle contractility is important for obtaining accurate corticospinal excitability data in exercise studies which utilize applied TMS at different time points [9].

##### Primary outcome: corticospinal excitability (CSE)

CSE will be measured using a single pulse TMS protocol. Two blocks of 25 stimulations, per hemisphere, that are elicited at an intensity of 120% of the resting RMT will be delivered over the FDI “hotspot” at rest and during an isometric contraction performed at 10% of the maximal force. This number of stimulations is sufficient to obtain a reliable measure of CSE using TMS [66]. Each stimulation will be applied 5s apart to reduce the effects of repetitive TMS on excitability [67]. A total of 50 stimulations will be averaged to obtain the composite MEP amplitude [9, 68]. MEP amplitude is examined because it can predict exercise-induced improvements in procedural memory and skill retention in healthy subjects [9] and motor recovery in stroke [8].

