### Hypotheses

We hypothesize that HIIT will be more effective in promoting neuroplasticity. HIIT will increase the excitability of upper limb representational areas on M1 of the lesioned hemisphere. This will lead to a reduction in the imbalances in M1 excitability that is typically observed in chronic stroke [43, 44]. Based on previous findings [22], we will also expect that the increases in M1 excitability in the lesioned hemisphere after HIIT will be partially mediated by a reduction in intracortical inhibition [45], which is a marker that has been described to increase post-stroke, negatively affecting recovery [8]. HIIT is also expected to be more effective in improving cardiovascular measures of resting BP, arterial stiffness, and VO_2_peak [32, 35]. We predict that after a period of 8 weeks post-termination of the training program (T2), these improvements in neuroplasticity and cardiovascular health will be maintained after to a greater extent in the HIIT group, in comparison to the participants in the MICT group.

We also anticipate greater improvement in walking speed [46], and motor learning post-HIIT, due to an increase in neuromuscular recruitment due to high-intensity exercise, and the aforementioned changes in neuroplasticity, respectively [22]. In contrast, we will also expect a similar improvement in walking capacity in response to either HIIT or MICT. Additionally, responses of motivation and enjoyment will be similar in both groups.

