### Sample size estimation

Based on previous data [21] and using a linear mixed model, we estimated that we would require 32 participants per group (*n* = 64 total) to detect a 5% increase at T1 in the resting MEP amplitude and intracortical inhibition of the affected hemisphere’s M1 in the HIIT group. An increase of 5% is associated with improved motor function in stroke [2]; therefore, we will consider this difference between HIIT and MICT groups to be clinically significant. The statistical package G*Power was used to determine the sample size required to obtain a power of 80% (alpha < 0.05). We have increased the sample size to 40 per group (*n*=80 total) to accommodate for a 20% attrition rate.

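### The primary outcome is defined as a composite MEP with no primary state or hemisphere named, whereas the sample size rests on the resting MEP of the affected hemisphere

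*Protocol article*

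**What the plan says.** All references are to the protocol article.

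- **Primary outcome: corticospinal excitability (CSE).** "Two blocks of 25 stimulations, per hemisphere, that are elicited at an intensity of 120% of the resting RMT will be delivered over the FDI", and this is done "at rest and during an isometric contraction performed at 10% of the maximal force". The summary is then fixed: "A total of 50 stimulations will be averaged to obtain the composite MEP amplitude". The section does not say which state or which hemisphere is primary.
- **Neuroplasticity, under Primary outcome.** "We will also apply TMS on both hemispheres", with the stated purpose of assessing interhemispheric imbalance.
- **Hypotheses.** "HIIT will increase the excitability of upper limb representational areas on M1 of the lesioned hemisphere".
- **Sample size estimation.** 32 per group are needed "to detect a 5% increase at T1 in the resting MEP amplitude and intracortical inhibition of the affected" hemisphere, with 80% power and alpha 0.05, raised to 40 per group for 20% attrition. Intracortical inhibition is listed elsewhere as a secondary outcome.
- **General TMS procedures.** "Electrical stimulation over the median nerve (FDI) will be used to assess changes in muscle contractility", and "normalizing MEP amplitude to muscle contractility is important for obtaining accurate corticospinal excitability data in exercise studies" that apply TMS at several time points. The CSE section does not say whether the primary MEP is the normalised one.

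**The concern.** The section that defines the primary outcome and the section that justifies the sample size describe different variables. The first gives a composite over stimulations delivered in two states. The second concerns one state in one hemisphere, together with a secondary outcome. The Hypotheses section points to the lesioned hemisphere but does not settle the state.

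Two things are at stake. The power claim may not carry over to the variable that is analysed. The choice of state, and on one reading of hemisphere, also stays open in the very section that should close it. A later analysis plan could choose between the two descriptions, but it could not make both true.

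**Working it through.** **1. Pulse count.** Two blocks of 25 give 2 × 25 = 50 per hemisphere, or 100 over both. A 50-pulse average is therefore formed within a hemisphere. Two readings remain:

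- (a) One block per state: 25 rest + 25 contraction = 50. This is the natural count. The composite mixes the two states and is not a resting MEP.
- (b) Two blocks per state: 50 pulses in each state. This gives 2 states × 2 hemispheres = 4 CSE values per visit, and the CSE section selects none of them.

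On neither reading does the CSE section define the variable used in the sample size section.

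**2. The plan's own figure.** The attrition step reproduces: 32 / (1 − 0.20) = 40 and 64 / 0.80 = 80. The 32 itself can be neither confirmed nor refuted, because no SD or within-person correlation is given. Solving backwards for a two-sided 5% two-group comparison:

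- Normal approximation: d = (1.960 + 0.842) × √(2/32) = 0.700, so a 5% difference implies an SD of 5 / 0.700 ≈ 7.1%.
- t-test: d = 0.711, SD ≈ 7.0%.
- One-sided: d ≈ 0.62 to 0.63, SD ≈ 8.0%.

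These are implied values, not figures from the protocol, which cites a linear mixed model and earlier data.

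**3. What reading (a) could do to power (illustration).** The assumptions, none of them from the protocol, are:

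- d = 0.700 for the resting MEP
- composite = (rest + contraction) / 2
- contraction SD equal to k times the resting SD, k = 1 to 3
- rest–contraction correlation ρ = 0.3 to 0.7
- contraction effect equal to f times the resting effect, each in its own SD units

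Then

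d_c = d(1 + fk) / √(1 + k² + 2ρk), power at 32 per group ≈ Φ(4·d_c − 1.96), where 4 = √(32/2).

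Example: k = 1, ρ = 0.5, f = 0 gives d_c = 0.700 / √3 = 0.404 and power Φ(−0.34) ≈ 37%.

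| Contraction response | Composite d | Power at 32 per group | n per group for 80% |
|---|---|---|---|
| None (f = 0) | 0.19 to 0.43 | 11% to 41% | 84 to 455 |
| Half (f = 0.5) | 0.47 to 0.65 | 46% to 74% | 37 to 73 |
| Equal (f = 1) | 0.74 to 0.87 | 84% to 94% | 21 to 29 |

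The last row exceeds 80% because averaging two imperfectly correlated measures that respond alike reduces noise. The direction of the change thus depends on quantities that the protocol does not give.

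**The case against.** The best defence is that the pieces already point one way. The hypothesis names the lesioned hemisphere, the sample size names the resting MEP of the affected hemisphere, and the analysis section makes T1 the focus. The unaffected side serves the imbalance question. The composite is referenced to earlier work that is not shown, and an article may leave details of the analysis variable to a fuller document. This narrows the gap but does not close it. The CSE section is not silent: it prescribes a composite, and nothing reconciles that with the sample size section.

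Several stronger readings are tempting, and the text does not support them:

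- **That the two hemispheres are averaged together.** Pulses are counted per hemisphere. The gap is only that no hemisphere is named as primary.
- **That only the resting MEP was powered.** The sample size section also names intracortical inhibition.
- **That power collapses.** If contraction MEPs are k times as large as resting ones (k = 1 to 5) and do not change, a 5% rise dilutes to 5 / (1 + k), that is 2.5% to 0.8%. Power would then run from about 29% to below 10%. This also needs the composite to keep the resting relative SD, which with equal relative SDs in the two states means a correlation of 1. If both states rise by 5%, there is no dilution.
- **That the false-positive risk is 18.5%.** 1 − 0.95⁴ = 0.185 treats four correlated measures as independent and ignores the pointers to the affected hemisphere. If only the state is open, the bound is 1 − 0.95² = 9.75%.
- **That the primary MEP is unnormalised.** The general procedures already point to normalisation. The CSE section simply does not restate it.
- **That 32 per group is wrong.** Nothing here shows that.

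**Conclusion.** The point holds as a mismatch of definition. Followed literally, the CSE section yields a primary outcome that the stated 80% power does not describe, or several candidates with none chosen. This conclusion needs no assumption beyond the text.

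The size of the consequence is conditional. Over the ranges assumed above, power at 32 per group could lie anywhere from 11% to 94%, depending on the SDs, the correlation and the contraction response. The fair statement is that 80% is not shown to apply, not that it has been lost. Because the primary outcome carries the trial's main comparison, its definition should be settled before analysis.

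**What to change.** In the CSE section, name one primary variable: the resting MEP amplitude of the affected-hemisphere FDI at T1, at 120% RMT. State how many resting pulses are averaged, and that the amplitude is normalised to muscle contractility as the general procedures indicate. Analyse contraction MEP, the unaffected hemisphere and the interhemispheric imbalance separately as secondary outcomes, not averaged into the primary.

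In the sample size section, refer to that one variable, give the SD used, and keep intracortical inhibition as secondary. The 32 per group (40 with attrition) then needs no change, since the resting affected-hemisphere MEP is already part of its stated basis.

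The cost is a protocol amendment, notified to the investigators, ethics boards and registry as the section on protocol modifications requires, and made before analysis. It assumes that rest and contraction blocks can be separated in the recorded data, which the protocol does not state.

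Two minor items can be checked in the same edit: the nerve named for FDI stimulation, and the RMT criterion, which appears in a length unit (0.05 μm) and may be only a typographical slip. Neither carries this point.

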### Secondary outcomes

#### Neuroplasticity

##### Secondary outcome

Short intracortical inhibition and intracortical facilitation (SICI and ICF)

SICI and ICF will be measured using a paired-pulse TMS protocol that will use a conditioning stimulus of 80% RMT, followed by a supra-threshold stimulus (120% RMT) delivered at rest after 2.5ms (inhibition) and 12ms (facilitation), respectively. These intervals between stimuli capture changes in excitability after motor learning [69] and are susceptible to change with exercise in people with chronic stroke [22]. The amplitude of the MEP elicited by the send stimulus normalized to the MEP amplitude at baseline will provide an estimate of inhibition and facilitation [45]. A total of 25 paired pulses (separated by 2s), per hemisphere, will be delivered at the FDI. Our laboratory has used these measures of excitability in a previous study to investigate the effects of a single bout of HIIT in individuals with chronic stroke [22]. ICF and SICI are important markers of neuroplasticity, specifically related to motor learning processes [45, 70], and have been used to predict motor recovery post-stroke [8].

#### Cardiovascular health

##### Secondary outcome — resting BP

Resting BP will be taken at the brachial artery of the less affected arm using an automated BP monitor. Two readings will be taken and averaged, and if values differ by > 5 mmHg, 2 more readings will be taken, and another average will be taken for 4 readings.

##### Secondary outcome — arterial stiffness

Central pulse wave velocity (PWV) represents the pulse wave propagation within the arterial tree [71] and is considered the gold standard marker of arterial stiffness. PWV will be measured using applanation tonometry, a non-invasive technique, to capture pulse waveforms at the carotid and femoral arteries. Central PWV will be calculated by the following equation: PWV= (meters, *D*)/(seconds, Δ*t*), where Δ*t* is the travel time of the propagated wave between carotid and femoral arteries, and *D* is the distance between the two locations being recorded [72]. An increase in PWV is associated with an increased risk of cardiovascular morbidity and mortality, respectively [73]. A previous study has described an inverse relationship between PWV and physical fitness post-stroke [74].

##### Secondary outcome — cardiorespiratory fitness

Cardiorespiratory fitness will be assessed by assessing the VO_2_peak of participants. VO_2_peak will be determined by a graded cardiopulmonary exercise test (CPET) on a recumbent stepper which has been validated for individuals with stroke [54] and has been used by our lab in a previous study [22]. Cardiovascular responses will be monitored using a 12-lead ECG and BP monitor. RPE will be recorded during the exercise test [75].  Each site will have a medical support team, including an on-call physician, in the case of any medical emergency during this assessment.

##### Secondary outcome – waist-hip ratio

Waist-hip ratio is among the strongest predictors of risk for stroke, independent of other vascular risk factors [76]. It will be determined from the waist circumference measured at the level of the umbilicus, and hip circumference will be taken at the level of the greater trochanters. Markers of abdominal obesity are easily measured in clinical settings and are stronger predictors of cardiovascular events [77, 78] than body mass index.

#### Motor function

##### Secondary outcome — gait speed

We will assess gait speed using a self-paced 10-m walk test (10mWT). Participants will be timed starting at the 4-m mark, up until the 8-m mark of the 10-m course. Speed over 6 m will provide the result for one trial. The average of both trials will be the outcome for gait speed. Participants will be permitted to use gait aids (e.g., walker, cane) during this assessment.

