### Objectives

The primary objective of this study is to compare the effects of 12 weeks of HIIT vs. MICT on neuroplasticity. Changes in neuroplasticity will be determined by examining different markers of excitability in upper limb representational areas of M1 with TMS. In addition, the secondary objectives of this study are to compare the effects of HIIT and MICT on measures of cardiovascular health, motor function, and psychosocial responses to exercise. Change in cardiovascular health will be measured by assessing resting BP, arterial stiffness, cardiorespiratory fitness (VO_2_peak), and waist-hip ratio. Psychosocial responses to exercise will examine the effect of HIIT vs. MICT on motivation and enjoyment in response to the respective exercise intervention. Motor function parameters of gait speed, walking capacity, and upper limb motor learning will also be assessed. The exercise interventions of HIIT and MICT will be conducted using a whole-body paradigm, utilizing recumbent steppers.

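### Gait speed is timed over a 4-m segment but reported as speed over 6 m; the two distances must be reconciled, since applying both literally would inflate speeds by 50%

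*Protocol article*

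**What the plan says.** The protocol article defines the measurement under the heading for the secondary outcome of gait speed. The test is a self-paced walk on a 10-m course. On the timed segment it says: "Participants will be timed starting at the 4-m mark, up until the 8-m mark of the 10-m course". On the distance that gives the speed, the next sentence says: "Speed over 6 m will provide the result for one trial". Two trials are then combined: "The average of both trials will be the outcome for gait speed".

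The Objectives section places the outcome among the secondary aims: "Motor function parameters of gait speed, walking capacity, and upper limb motor learning will also be assessed". The Hypotheses section gives it a direction, with greater improvement in walking speed expected after HIIT. The text gives no formula for speed, and no other section states the marks or the timed distance.

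**The concern.** The distance between the 4-m and 8-m marks is 4 m, so a time taken between them cannot be a time over 6 m. The measurement rule for a named outcome is therefore wrong as written, and a reader cannot tell whether a mark or the distance is at fault.

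What is at stake is the scale of the outcome. A speed in m/s is meaningful only if the distance in the numerator is the distance that was timed. If it is not, the mean speeds and the treatment effect in m/s are on a false scale and cannot be compared with gait speeds from elsewhere.

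Two features of the trial make this more than a wording matter. There are two sites, each of which has to apply the rule. According to the Trial status section, recruitment began in September 2019 and was ongoing, so some data were probably collected before the article appeared.

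**Working it through.** **Inputs**
- From the gait-speed section: start of timing at the 4-m mark, end of timing at the 8-m mark, distance for speed 6 m, mean of two trials.
- From the Sample size estimation section: 32 participants per group before allowance for attrition. This is used only in the power illustration.
- Assumed, not in the documents: true speeds of 0.4, 0.8 and 1.2 m/s, a true between-arm difference of 0.10 m/s, and a standard deviation of 0.20 m/s.

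**Step 1: reproduce the stated distance.** Timed distance = end mark − start mark = 8 − 4 = 4 m. The stated 6 m is not reproduced. On a 10-m course, marks at 2 m and 8 m give 8 − 2 = 6 m, and marks at 4 m and 10 m give 10 − 4 = 6 m. A change to either mark, or to the stated distance, would remove the conflict.

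**Step 2: size of the error if both sentences are applied literally.** Let t be the time for 4 m. True speed = 4/t; recorded speed = 6/t; ratio = (6/t)/(4/t) = 6/4 = 1.50, or +50%.

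| True speed (assumed, m/s) | Time for 4 m (s) | 6 m divided by that time (m/s) |
|---|---|---|
| 0.4 | 10.0 | 0.6 |
| 0.8 | 5.0 | 1.2 |
| 1.2 | 3.33 | 1.8 |

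Averaging two trials does not alter this: (1.5a + 1.5b)/2 = 1.5 × (a + b)/2. A true between-arm difference of 0.10 m/s would read 0.10 × 1.5 = 0.15 m/s.

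**Step 3: what the factor does to inference.** Suppose it applies to everyone at every visit.
- Percentage change: (1.5a − 1.5b)/(1.5b) = (a − b)/b, unchanged.
- Standardised difference: (1.5 × 0.10)/(1.5 × 0.20) = 0.15/0.30 = 0.10/0.20 = 0.5, unchanged.
- Power with 32 per arm: 0.516 for a difference of 0.10 with SD 0.20, and 0.516 for 0.15 with SD 0.30.

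The p-value is unchanged for the same reason: estimate and standard error are multiplied by the same constant.

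**Step 4: size of the error if one figure is a misprint.** If 4 m is timed and 4 m is the divisor, or 6 m is timed and 6 m is the divisor, the ratio is 1.00 and the bias is 0%.

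**The case against.** A reader might infer that the trial overstates every gait speed by 50%. The document does not support that. It gives no formula and never says that 6 m is divided by the time for 4 m. The phrase about speed over 6 m could equally mean that 6 m is timed and one mark is misprinted, in which case nothing is biased. This objection stands: the contradiction is certain, but the 50% is conditional.

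A reader might also infer that the comparison of HIIT with MICT is compromised. It is not, on the literal reading, because a constant multiplier in both arms and at all visits leaves the test of the walking-speed hypothesis as it was. The article also sets no target difference or threshold in m/s that an inflated value could wrongly pass. This stands too, and it confines the harm to reported speeds and differences in m/s.

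A third tempting inference is a site artefact. If one site's timed distance and divisor disagreed while the other's matched, their speeds would differ by a factor of 1.5. Nothing in the document shows that the sites differ. The Discussion commits the steering committee to training and standardised assessment technique at both. Sites that used different but internally consistent distances would not produce such a factor. Randomisation is 1:1 and stratified by site, so a scale difference would fall on both arms and would mainly add noise and blur the pooled m/s scale. The possibility is a reason to ask the sites, not a finding in itself.

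None of this removes the defect. Both sentences are intact prose, and the article does not leave the rule to another document: it states the rule, and the rule contradicts itself.

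**Conclusion.** The point holds as a contradiction in the measurement rule for a secondary outcome: 4 m is timed, and 6 m is given as the distance for speed.

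The effect on the data is one of two cases, and the document does not say which. If both sentences are carried out literally, absolute speeds and between-arm differences in m/s read 50% too high, while percentage changes, standardised effects, p-values and power are unaffected. This assumes one procedure for all participants, visits and sites. If one figure is a misprint and practice is consistent, the effect is nil.

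The weight is moderate. The primary outcome is corticospinal excitability and the sample size rests on MEP amplitude and intracortical inhibition, so neither depends on gait speed. The text should nevertheless be corrected and past practice confirmed before any gait-speed result in m/s is reported.

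**What to change.** 1. Ask both sites which marks they have timed between, and which distance they have divided by, since recruitment began in 2019. Ask whether this was the same at T0, T1 and T2.
2. Correct the text so that marks and divisor agree and match that practice: a 6-m segment (such as 2 m to 8 m, or 4 m to 10 m) with a divisor of 6 m, or 4 m to 8 m with a divisor of 4 m. Apply one rule at both sites.
3. Only if timed distance and divisor differed, correct the affected speeds. Where 6 m was divided by the time for 4 m, multiply by 4/6; for example, 1.20 × 4/6 = 0.80 m/s. Alternatively, recompute from recorded times. The article mentions paper case report forms but does not say whether they hold the raw times, so the known factor is the fallback. Make the correction by site and visit wherever practice varied.

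The cost is one corrected sentence and a query to each site, with a simple rescaling if a mismatch is found. The design, the sample size and the primary analysis do not change.
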